**Methods:**

This study protocol describes the development and validation of a prediction model for the longitudinal progression of renal function decline in Caucasian patients with type 2 diabetes mellitus (DM2). For development and internal-external validation, two prospective multicenter observational studies will be used (PROVALID and GCKD). The estimated glomerular filtration rate (eGFR) obtained at baseline and at all planned follow-up visits will be the longitudinal outcome. Demographics, clinical information and laboratory measurements available at a baseline visit will be used as predictors in addition to random country-specific intercepts to account for the clustered data. A multivariable mixed-effects model including the main effects of the clinical variables and their interactions with time will be fitted. In application, this model can be used to obtain personalized predictions of an eGFR trajectory conditional on baseline eGFR values. The final model will then undergo external validation using a third prospective cohort (DIACORE). The final prediction model will be made publicly available through the implementation of an *R shiny* web application.

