### Objective

The main objective of the planned analysis is the development, internal-external, and external validation of a personalized prediction model for eGFR loss per year in Caucasian people with DM2. It is based on clinical information and laboratory measurements recorded at baseline. A secondary aim is the implementation of the externally validated prediction model as a publicly available web application to facilitate general applicability in clinical care based on data from recent eras using modern therapy.

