### Study outcome

The primary outcome of interest for the study is the annual decline in renal function, derived through the use of at least 3 follow-up measurements of eGFR. The eGFR values will be calculated by the equation of the Chronic Kidney Disease Epidemiology Collaboration (CKD-EPI) using the patient’s race, sex, age, and serum creatinine level [21].

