### Model evaluation, performance, and external validation

An analysis of the conditional residuals will be conducted to check correct model specification, e.g., normality, linearity, and homoscedasticity of the error terms. Next, the importance of each independent variable will also be evaluated by the drop in the adjusted *R*^2^, i.e., the loss in estimated explained variation when the respective predictor is removed from the model.

The performance of the prediction model will be evaluated by an internal-external validation procedure to obtain a reliable assessment of its generalizability of prediction to unseen data [29]. The unit for the non-random data splitting will be the six countries within the PROVALID and GCKD studies (GCKD: Germany; PROVALID: Austria, Hungary, Netherlands, Poland, and Scotland) such that for each iteration, one regional group with its study participants are withheld from model training and then used for testing.

The prediction performance will further be assessed through:
Discrimination in terms of Kendall-tau-b concordance correlation coefficients at each time point, i.e., the concordance of the predicted eGFR values at time *t* obtained by Eq. (4) and the actual observed eGFR in each pair of patientsCalibration in terms of the slope of the calibration curve by
I.Regressing the predicted eGFR on the actual eGFR values at each time pointII.Plotting the estimated mean risk for fast progression per decile against the observed ratio of fast progression within each risk decileExplained variation in terms of adjusted *R*^2^, i.e., the proportion of explained variability in the outcome by the independent variables

The external validity of the model will be examined by applying the final prediction model to the DIACORE study cohort and evaluating the three performance measures outlined above.

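### Discrimination is scored only on eGFR level, so no planned statistic measures how well the model ranks patients on annual decline, its primary outcome

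*Protocol article*

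**What the plan says.** The Objective section of the protocol article describes a "personalized prediction model for eGFR loss per year in Caucasian people with DM2". The Study outcome section agrees: "The primary outcome of interest for the study is the annual decline in renal function". The Web implementation section promises users the predicted yearly decline, the share of people with a larger predicted loss, and a relative risk of rapid decline. It also promises the predicted eGFR value at 1 to 5 years. The abstract names eGFR itself, "obtained at baseline and at all planned follow-up visits will be the longitudinal outcome".

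The section on model evaluation, performance and external validation lists three kinds of measure:

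- Discrimination: "Discrimination in terms of Kendall-tau-b concordance correlation coefficients at each time point, i.e., the concordance of the predicted eGFR values at time" t, from Eq. (4), with the observed eGFR.
- Calibration, in two parts. Part I regresses predicted on observed eGFR at each time point. Part II plots mean predicted risk of fast progression by decile against the observed proportion.
- Adjusted R², defined as "the proportion of explained variability in the outcome by the independent variables".

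The same measures are applied to DIACORE. Separately, "the importance of each independent variable will also be evaluated by the drop in the adjusted" R².

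**The concern.** The declared target is a slope, but the only ranking statistic is computed on level. Under Eqs. (2) to (4), each updated prediction carries the patient's own baseline eGFR. Patients differ far more in level than in what a few years of differing decline add or remove, so a high tau-b mostly shows that baseline eGFR predicts later eGFR. A model with no ability to tell fast from slow decliners could score almost as well as one that has it. The tool is meant to identify people at risk of rapid loss, and it will be open to patients as well as clinicians. A published tau near 0.7 would tell them little about that use.

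**Working it through.** **Figures the plan gives.** The plan states no expected tau. Its R² values stand in the Sample size section, with a mean of 78.4 and an SD of 21.4 for eGFR level. The minimum sizes there (271, 3048, 1569, 903) reproduce exactly as the smallest n with 1 + (p − 2)/(n ln(1 − R²app)) ≥ S, where R²app = (R²(n − p − 1) + p)/(n − 1) and p = 13. They are not in dispute. They suggest that R² is thought of on the level scale.

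**From document figures alone.** The Introduction calls a loss of 1 mL/min/1.73m² per year standard under current therapy, and the default rapid-decline cutpoint is a loss of 3. Two such patients differ by 2 × 2 = 4 at year 2, or 4/21.4 = 0.19 SD of level. At year 5 they differ by 2 × 5 = 10, or 10/21.4 = 0.47 SD.

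**Model calculation.** These inputs are assumed, because the documents do not give them: random-intercept SD 18, residual SD 6, slope SD 1.5 per year, predictable part of the slope SD 0.8 (0.64/2.25 = 28% of slope variance), and no intercept-slope correlation. The implied baseline SD is √(324 + 36) = 19.0, a little below the plan's 21.4.

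- The weight in Eq. (2) is 324/360 = 0.9.
- The variance of observed eGFR at year t is 360 + 2.25t².
- For a common-slope prediction, ρ² = 0.9 × 324/(360 + 2.25t²) = 291.6/(360 + 2.25t²).
- For a slope-predicting model, ρ² = (291.6 + 0.64t²)/(360 + 2.25t²).
- Under normality, tau = (2/π) arcsin ρ.

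| Year | ρ² common slope | ρ² slope-predicting | tau common slope | tau slope-predicting | Gain |
|---|---|---|---|---|---|
| 1 | 0.805 | 0.807 | 0.709 | 0.710 | 0.001 |
| 2 | 0.790 | 0.797 | 0.697 | 0.703 | 0.005 |
| 5 | 0.701 | 0.739 | 0.631 | 0.659 | 0.027 |
| 10 | 0.498 | 0.608 | 0.499 | 0.569 | 0.070 |

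Scored against the true slope, the second model has tau = (2/π) arcsin √0.284 = 0.36. The common-slope model cannot rank patients on decline at all.

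**Range.** A grid with baseline SD 21.4 varied residual SD from 5 to 10, slope SD from 1.5 to 3, predictable share from 10% to 40%, intercept-slope correlation from −0.3 to 0.3, and baseline variance explained by covariates from 0.3 to 0.7. The gain in tau has median 0.008 (maximum 0.030) at year 2 and median 0.035 (range 0.007 to 0.110) at year 5. The maximum occurs with residual SD 5, slope SD 3, 40% predictable and correlation −0.3. Tau for the true slope runs from 0.20 to 0.47 over the grid.

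**Time zero.** The model is indexed from t = 0, and tau-b is planned at each time point. Read literally, the baseline value is then compared with a prediction built from it. With no covariates that prediction is the mean plus 0.9 times the patient's deviation from it, so tau is 1 by construction.

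**Choice of comparator for decline.** By Eqs. (2) and (3) the predicted slope depends on the observed baseline. Change from baseline contains the same baseline error with opposite sign. Take the SDs above, no covariate information on slope, and intercept-slope covariance c = r × 18 × 1.5.

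- Against the true slope: ρ = |c|/(√360 × 1.5).
- Against change at year 2: ρ = sign(c)(2c − 36)/(√360 × √81), since 4 × 2.25 + 72 = 81.
- Against a slope from annual visits 1 to 5: ρ = |c|/(√360 × √5.85), since 2.25 + 36/10 = 5.85.

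| r | c | tau, true slope | tau, change at year 2 | tau, post-baseline slope |
|---|---|---|---|---|
| −0.05 | −1.35 | 0.03 | 0.15 | 0.02 |
| +0.30 | 8.1 | 0.18 | −0.07 | 0.11 |

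Simulation agrees to within about 0.02. Change from baseline can flatter a nearly useless model or reverse the sign. The post-baseline slope keeps the right sign.

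**The case against.** The strongest reply is that the plan already tests decline. Calibration part II concerns the risk of fast progression and is repeated in DIACORE. In a simulation with residual SD 7, slope SD 2 and 30% predictable, a common-slope model shows one flat risk of about 0.23, while a slope-predicting model spreads from 0.02 to 0.59 across deciles. This stands. A reader might infer that the study cannot answer its own question about yearly loss, and the document does not support that. Still, a decile plot shows agreement and spread and yields no ranking statistic.

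Second, eGFR level is a legitimate target, since it is the modelled outcome and the first output of the web tool. This stands too, and the level measures should remain.

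Third, adjusted R² is defined through the independent variables, so the baseline-update argument does not carry over to it. That R² is on level is itself an inference from the modelled outcome and the Sample size section. Covariate-only R² also gains little from slope prediction in the grid (medians 0.009 at year 2 and 0.046 at year 5), but that is a separate and weaker argument. It is also tempting to say that age and sex will dominate the importance ranking because they enter the eGFR equation. Nothing in the documents quantifies this.

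Fourth, the Discussion warns that individual slopes are estimated very imprecisely. That is true. It limits how large a slope tau can be, but it does not make level tau a substitute.

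Finally, tau is reported separately by time point, so a trivial value at t = 0 does not contaminate the others.

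**Conclusion.** The point holds for discrimination. The plan ties its only ranking statistic to eGFR level, while its objective, primary outcome and several user outputs concern decline. That is a stated choice, not detail left to a fuller document. Under the assumed SDs the level tau moves by about 0.00 to 0.03 through year 5 between a model with real slope prediction and one with none. The difference is about 0.07 at year 10, which matters because GCKD follows patients for up to 10 years and DIACORE for at least 10. It is about 0.11 at year 5 in the extreme corner of the grid. So near-equality holds for the early visits and most scenarios, but not everywhere. The sizes rest on slope and residual SDs that the documents do not give; the mismatch itself does not. It should be corrected before validation is run, and it does not invalidate the model or the rest of the evaluation.

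**What to change.** In the evaluation section:

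1. Keep tau-b, calibration and R² on level as validation of the eGFR-value output, and omit t = 0 for tau-b.
2. Report the level measures next to a pre-specified benchmark: baseline eGFR with the common mean slope.
3. Add discrimination for decline: tau-b or a C-statistic of the predicted slope (already defined after Eq. (4)) against each patient's slope from post-baseline visits only, in each held-out country and in DIACORE. The Target population rule of three creatinine visits including baseline guarantees at least two such visits. Do not use raw change from baseline.
4. Beside the drop in R², report each predictor's contribution to the predicted slope through its time interaction.

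This needs no new data and no change to the model. Calibration part II already requires an observed decline for each patient. The cost is less impressive figures, because observed slopes are noisy. With the SDs above, a slope tau of 0.36 shrinks to (2/π) arcsin √(0.64/5.85) = 0.21 with five annual post-baseline visits. With only two visits two years apart, the observed slope variance is 2.25 + 72/4 = 20.25 and tau falls to (2/π) arcsin √(0.64/20.25) = 0.11. The report should state this attenuation.

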### Prediction model development

People adhering to the inclusion and exclusion criteria from either the PROVALID or GCKD study will be considered for model building. Mixed-effects modeling accounts for the dependencies between repeated measurements per person over time and the similarity among people belonging to the same study cohort, hence they are commonly employed to analyze longitudinal and clustered data. Here, we will consider hierarchically nested random effects for the country and people within a country, such that the heterogeneity of eGFR trajectories between the five countries within the development cohort can be modeled appropriately [26]. More specifically, we will use random effects for the intercept and the slope of the repeated eGFR measurements over time and an additional random intercept for the country. We will include the baseline eGFR value in the outcome vector to provide more stable estimates of variability. When applying the model, any available eGFR measurements of an individual for whom eGFR trajectory predictions should be obtained can be used to improve predictions. A similar approach has been conducted by Selles et al. [27] to develop a prediction model not only able to deal with multiple measurements per subject but also able to allow these repeated clinical measurements to contribute to the prediction of an unseen individual. The set of clinical variables outlined in Table 2 will constitute the fixed effects. Automated variable selection will not be conducted as the set of predictors was chosen by background knowledge. Furthermore, due to the large sample size available for estimation overfitting is expected to be minimal, such that further regularization of the predictor effects will be omitted. Clinically relevant pairwise interactions of the independent variables with time will be investigated and added if their inclusion improves the prediction accuracy of the model as determined by the Akaike information criterion (AIC). Any model misspecification, e.g., regarding functional forms of the variables in the model, will be assessed using a plot of the marginal residuals versus the individual variables. Variables with non-linear relationships with the outcome as exhibited by these residual plots will then be modeled using restricted cubic splines to improve the model fit [28]. In addition, the relevance of the inclusion of such non-linear terms for improving the model fit will be evaluated in terms of the AIC.

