More formally, the model for the continuous eGFR values *Y*_*it*_ at time point *t* (*t* = 0, …, *T*) for subject *i* (*i* = 1, …, *n*) is defined by
1$$ {\mathrm{Y}}_{\mathrm{i}\mathrm{t}}={\upbeta}_0+{\mathrm{a}}_{\mathrm{i}}+{\upbeta}_1X+{\upbeta}_2\mathrm{t}+{\upbeta}_3\mathrm{tX}+{\mathrm{b}}_{0\mathrm{i}}+{\mathrm{b}}_{1\mathrm{i}}\mathrm{t}+{\upepsilon}_{\mathrm{i}\mathrm{t}}, $$

with normally distributed residuals $$ {\epsilon}_{it}\sim N\left(0,{\sigma}_{\epsilon}^2\right) $$ with mean 0 and variance $$ {\sigma}_{\epsilon}^2 $$, random country-specific intercepts assumed to be *a*_*i*_~*N*(0, *τ*^2^), the random coefficients (*b*_0*i*_, *b*_1*i*_)~*MN*(0, *G*) (where MN denotes the bivariate normal distribution with an unspecified covariance matrix G, defined by the diagonal elements $$ {\upsigma}_0^2 $$ and $$ {\upsigma}_1^2 $$ and the off-diagonal σ_01_) and the vector of regression coefficients for the clinical independent variables *β* = (*β*_0_, *β*_1_, *β*_2_, *β*_3_). It should be noted that for simplicity of description, we here consider a single clinical predictor variable *X*, where *β*_1_ and *β*_3_ represent the regression coefficients corresponding to the clinical predictor variable and its interaction with time. Without loss of generality, more clinical predictors can be added, each with two regression coefficients for the baseline effects of the predictor and the corresponding interaction with time. When considering restricted cubic splines for a variable, this variable will be represented by several corresponding basis functions in (1).

Model (1) allows to prognosticate baseline and follow-up values of eGFR for a new person *j* given the value of the clinical predictor *X*, assuming that for that new person the random intercept and slope are equal to their expected values of 0. Further, we will assume the expected random country effect of *a*_*j*_ = 0 for the prediction of eGFR in a new individual. In order to incorporate a baseline eGFR measurement *y*_*j*0_ into the prediction, a best linear unbiased predictor (BLUP) of the individual’s random effects can be obtained through the posterior distribution of the random effects. The random intercept for that new subject *j* is then estimated by
2$$ {\hat{\mathrm{b}}}_{0\mathrm{j}}=\frac{\upsigma_0^2\left({\mathrm{y}}_{\mathrm{j}0}-{\hat{\mathrm{y}}}_{\mathrm{j}0}\right)}{\upsigma_0^2+{\upsigma}_{\upvarepsilon}^2}, $$

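### Read literally, the scoring rule includes baseline, where the Eq. (4) prediction contains the very eGFR value it is scored against

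*Protocol article*

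**What the plan says.** Four statements in the protocol article bear on this.

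- **Outcome.** The abstract's Methods say that eGFR "obtained at baseline and at all planned follow-up visits will be the longitudinal outcome". Under Prediction model development the article adds: "We will include the baseline eGFR value in the outcome vector to provide more stable estimates of variability". Model (1) runs its time index from t = 0 to T, and the text below it says the model can forecast baseline as well as follow-up eGFR.
- **Prediction.** The same section introduces the update with "In order to incorporate a baseline eGFR measurement". Eq. (2) estimates a new person's random intercept from the observed baseline value, Eq. (3) derives the random slope from that intercept, and Eq. (4) adds both to the fixed-effects prediction.
- **Scoring.** Under Model evaluation, performance, and external validation, discrimination is "Discrimination in terms of Kendall-tau-b concordance correlation coefficients at each time point", defined as "the concordance of the predicted eGFR values at time *t* obtained by Eq. (4) and the actual observed eGFR". The first calibration item regresses predicted on actual eGFR, again for every time point.
- **Reach.** The procedure is run on each held-out country, and external validation in DIACORE consists of "evaluating the three performance measures outlined above".

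No statement limits scoring to visits after baseline.

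**The concern.** Taken together, these statements make t = 0 a scored time point. At that point the prediction has been built from the value it is compared with. Withholding a country or moving to DIACORE does not help, because what leaks is the test person's own baseline measurement and not information from the training data.

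A tau-b at t = 0 obtained this way says nothing about the stated objective, eGFR loss per year, or about the web tool's 1- to 5-year forecasts. A model with no information on change would also score very well there. At stake is a flattering but empty discrimination entry, and a distorted calibration entry, in each performance table that supports releasing the tool.

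**Working it through.** **The article's own figures.** It gives no performance figure to reproduce. Its computed figures are the sample sizes. Applying the shrinkage criterion 1 + (p − 2)/(n·ln(1 − R²app)) ≥ S with p = 13 returns 271, 3048, 1569 and 903, all as stated. The point does not depend on them. The Sample size section serves only as the source of the total SD and R² below.

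**Algebra.** Write λ = σ0²/(σ0² + σε²). At t = 0 the slope term in Eq. (4) vanishes. Putting Eq. (2) into Eq. (4) gives

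ỹ_j0 = ŷ_j0 + λ(y_j0 − ŷ_j0) = (1 − λ)ŷ_j0 + λ·y_j0.

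The observed value y_j0 is thus part of its own prediction for any positive variances. Assumptions affect only the size.

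**Inputs for the size.**
- Total SD 21.4 and R² 0.3, from Sample size. R² is used here as the fixed-effects share of baseline variance, which is an assumption.
- Residual SD σε of 4 to 10. This is assumed, as the article gives none.
- Country variance is not separated out, and joint normality is assumed.

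**Formulas.** V = 21.4² = 457.96. Vf = 0.3 × 457.96 = 137.39. σ0² + σε² = 457.96 − 137.39 = 320.57.
- Var(ỹ_j0) = Vf + λσ0².
- Covariance with the same y_j0: Vf + λ(σ0² + σε²) = Vf + σ0².
- Covariance with an independent replicate baseline: Vf + λσ0².
- tau = (2/π)·asin(r).

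**Worked case, σε = 8.** σ0² = 320.57 − 64 = 256.57 and λ = 256.57/320.57 = 0.800. Var(ỹ_j0) = 137.39 + 205.35 = 342.74. The covariance with the same value is 137.39 + 256.57 = 393.96.
- Same value: r = 393.96/√(342.74 × 457.96) = 0.9944, tau = 0.933.
- Replicate: r = 342.74/√(342.74 × 457.96) = 0.8651, tau = 0.665.
- Slope of predicted on actual (the article's direction): 393.96/457.96 = 0.860, against 342.74/457.96 = 0.748 for the replicate.
- Slope of observed on predicted: 393.96/342.74 = 1.149, against 1.000 for the replicate.

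**Range at R² 0.3.**

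| Residual SD | λ | tau, same value | tau, replicate | Excess | Predicted on actual: same / replicate | Observed on predicted: same / replicate |
|---|---|---|---|---|---|---|
| 4 | 0.950 | 0.985 | 0.832 | 0.153 | 0.965 / 0.932 | 1.036 / 1.000 |
| 6 | 0.888 | 0.964 | 0.748 | 0.216 | 0.921 / 0.852 | 1.082 / 1.000 |
| 8 | 0.800 | 0.933 | 0.665 | 0.268 | 0.860 / 0.748 | 1.149 / 1.000 |
| 10 | 0.688 | 0.885 | 0.585 | 0.300 | 0.782 / 0.631 | 1.238 / 1.000 |

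**Higher R².** The article expects more than 0.3 and also names 0.5 and 0.7. At 0.5, tau is 0.977 to 0.827 against 0.833 to 0.603 for the replicate. At 0.7 it is 0.965 to 0.743 against 0.835 to 0.647. Over all three R² values the excess runs from about 0.10 to 0.30.

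**Simulation check.** With 6,000 people, yearly visits to year 5, and an assumed slope SD of 1.5, mean slope of −1.5 and zero intercept–slope covariance, tau at t = 0 agrees with the closed form (0.985 at residual SD 4, 0.885 at residual SD 10). Over years 1 to 5 it runs from 0.825 to 0.730 and from 0.586 to 0.555 respectively. These later values are the same whether or not t = 0 is scored.

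**The case against.** The strongest reply is that scoring at baseline is inferred and not stated. The index from t = 0 defines the model for fitting, and baseline enters the outcome vector for a stated purpose, stabler variance estimates. Elsewhere baseline eGFR is an input to prediction, and the web output starts at year 1. An analyst might skip t = 0 without being told, and a list of scored visits can be left to an analysis plan.

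Part of this stands: a post-baseline reading is plausible, and the article never names baseline in its scoring rule. But the rule does name the predictor, Eq. (4), and the time points, all of them, without exception, in a text that counts baseline among the values the model forecasts. The literal reading is therefore open, and the text as written leads to it.

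The reply is also right about reach. A reader might infer several stronger claims that the article does not support:

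- **Overall performance is inflated.** Results are planned per time point, with no average or pooled Eq. (4) measure. A mean tau-b including t = 0 would be too high (in the simulation 0.815 against 0.781 at residual SD 4, and 0.623 against 0.571 at residual SD 10), but no such mean is planned.
- **A third of the scored values are circular.** That is the share for a person with the minimum of three visits. It has no bearing on statistics computed visit by visit.
- **Explained variation is inflated.** Adjusted R² is defined by the independent variables and is not tied to Eq. (4).
- **Calibration looks near-perfect.** It does not. In the article's direction the t = 0 slope is closer to 1 than the replicate slope but still 0.965 to 0.782. In the other direction it exceeds 1. Use of Eq. (4) for this item is the natural reading but is not stated.
- **Risk-decile calibration is affected.** It is not computed per time point and lies outside the point.

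**Conclusion.** The point holds in a limited form. Under the literal rule, the t = 0 tau-b is circular in every held-out country and in DIACORE. It exceeds the replicate-based value by about 0.15 to 0.30 at R² 0.3, and by about 0.10 to 0.30 across R² 0.3 to 0.7. The t = 0 calibration slope is distorted if it too uses Eq. (4).

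The circularity follows from Eqs. (2) and (4) alone. Its size rests on the assumed residual SD of 4 to 10, on treating R² as the fixed-effects share at baseline, and on normality. That t = 0 would be scored at all rests on combining the time index with the scoring rule. Everything reported for t > 0 stands, so this is a small defect in a stated rule and not a flaw in the validation design.

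**What to change.** In Model evaluation, performance, and external validation, state that tau-b and the per-time-point calibration slope based on Eq. (4) are computed at post-baseline time points only (t > 0), in each held-out country and in DIACORE. If baseline performance is wanted, score only the unconditioned fixed-effects prediction ŷ_j0 there and label it separately. Under the inputs above, its tau would be (2/π)·asin(√0.3) = 0.369 at R² 0.3.

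The cost is one sentence. No data, model or sample size changes, and the only loss is a flattering t = 0 entry.

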### Sample size

Overall, 13 predictors will be included in the prediction model. Guidelines regarding the minimum required sample size for the development of a new multivariable prediction model have been recently proposed by Riley et al. [22]. Using the accompanying R package “pmsampsize” with an assumed average value for eGFR of 78.4mL/min/1.73m^2^ and a standard deviation of 21.4 mL/min/1.73m^2^ [23] in the population, an anticipated *R*^2^ of the model of 0.3 [24] and a shrinkage factor of 0.9, the minimum sample size aimed at minimization of overfit and the precise estimation of the parameters of a prediction model with 13 predictors is 271. Further, since regularization is not taken into consideration in model development due to the abundance of data relative to the number of predictors, the computation with a shrinkage parameter of 0.99 results in a sample size of 3048 required subjects. However, a much larger *R*^2^ is expected, which is why a minimum sample size of 1569 is required for a *R*^2^ of 0.5 and 903 participants for 0.7, respectively. Nevertheless, the development cohort will comprise around 5800 subjects and thus will exceed the minimum required sample size by far.

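### The calibration slope for eGFR is defined the wrong way round: predicted is regressed on actual, so a perfectly calibrated model scores its R² instead of 1

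*Protocol article*

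**What the plan says.** All references are to the protocol article.

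- **Model evaluation, performance, and external validation.** Calibration is to be judged by the slope of the calibration curve. Item I obtains it by "Regressing the predicted eGFR on the actual eGFR values at each time" point. Item II is a separate plot, by decile, of estimated risk of fast progression against the observed proportion of fast progressors.
- **Same section, internal-external validation.** Each of six countries is held out in turn.
- **Same section, external validation.** The final model is applied to DIACORE by "evaluating the three performance measures outlined above", so the same slope is used there.
- **Prediction model development.** The prediction assessed is the fixed-effects value updated with the person's baseline eGFR, for which "a best linear unbiased predictor (BLUP) of the individual’s random effects can be obtained through the posterior distribution of the random effects".

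No target value or acceptance limit is given for the slope, and no other section states the opposite direction.

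**The concern.** Regressing A on B makes A the dependent variable. The stated regression therefore estimates the mean prediction given the observed eGFR. Calibration concerns the mean observed eGFR given the prediction.

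The two regressions agree only when prediction is perfect. With any residual variation, the noise in observed eGFR sits in the regressor and pulls the slope as written below 1, even for an ideal model. Read against the usual target of 1, a well-calibrated model looks poorly calibrated and an over-dispersed one can look ideal. If anyone later rescaled predictions to bring this slope to 1, they would make good predictions too extreme.

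The slope is the only calibration check the article specifies for the eGFR values themselves, and those are what the web tool will show for years 1 to 5.

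**Working it through.** **Inputs (Sample size section).** "Overall, 13 predictors will be included in the prediction model". The calculation is made "with an assumed average value for eGFR of 78.4mL/min/1.73m^2" and "a standard deviation of 21.4 mL/min/1.73m^2". The R² scenarios are 0.3 ("of the model of 0.3 [24] and a shrinkage factor of 0.9") and then 0.5 and 0.7 ("of 0.5 and 903 participants for 0.7, respectively").

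**Step 1. Reproduce the plan's own figures.** The article gives no calibration figure, but its sample sizes confirm the R² inputs. With p = 13, find the smallest n for which 1 + (p − 2)/(n·ln(1 − R²app)) reaches the shrinkage target, where R²app = (R²(n − p − 1) + p)/(n − 1). For R² = 0.3, target 0.9 and n = 271:

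- R²app = (0.3 × 257 + 13)/270 = 0.3337
- shrinkage = 1 − 11/(271 × 0.4060) = 0.900

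With a target of 0.99, the same formula gives 3048, 1569 and 903 for R² = 0.3, 0.5 and 0.7. All four sizes match the article.

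**Step 2. Perfectly calibrated predictions.** Let P be the prediction and Y the observed eGFR, with E(Y | P) = P. Then Cov(Y, P) = Var(P), and:

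- slope of Y on P = Cov/Var(P) = 1
- slope of P on Y (as written) = Var(P)/Var(Y) = R²
- intercept of P on Y = 78.4 × (1 − R²), where 0 is ideal

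**Step 3. Over-dispersed predictions.** Stretch the deviations of P from the mean by 1/R². The covariance becomes Var(P)/R² = Var(Y), and the prediction variance becomes Var(P)/R⁴ = Var(Y)/R². Then:

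- slope of P on Y (as written) = 1
- slope of Y on P = R²
- mean squared error = Var(Y)(1/R² − 1), against Var(Y)(1 − R²) for the calibrated model, with Var(Y) = 21.4² = 458

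| R² | Calibrated: slope as written | Calibrated: intercept as written | Calibrated: actual on predicted | Stretch factor | Stretched: slope as written | Stretched: actual on predicted | MSE calibrated / stretched |
|---|---|---|---|---|---|---|---|
| 0.3 | 0.30 | 54.9 | 1.00 | 3.33 | 1.00 | 0.30 | 321 / 1069 |
| 0.5 | 0.50 | 39.2 | 1.00 | 2.00 | 1.00 | 0.50 | 229 / 458 |
| 0.7 | 0.70 | 23.5 | 1.00 | 1.43 | 1.00 | 0.70 | 137 / 196 |

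A simulation of 1,000,000 subjects agreed to within sampling error.

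**Step 4. The article's own type of prediction.** Simulate model (1) with the updates in Eqs. (2) to (4). The article gives no variance components, so two sets were assumed. Both use a random-slope SD of 1.5, and fixed-effect SDs of 10 (level) and 0.7 (slope).

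| Assumed components | Slope as written, years 1, 2, 3, 5 | Actual on predicted |
|---|---|---|
| Random-intercept SD 15, error SD 7, covariance 0 | 0.76, 0.75, 0.73, 0.67 | 1.00 throughout |
| Random-intercept SD 12, error SD 8, covariance −3 | 0.64, 0.63, 0.61, 0.55 | 1.00 throughout |

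Hand check, first set, year 1:

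- Var(P) = 100 + 0.49 + 225²/274 = 285.3
- Var(Y) = 100 + 0.49 + 225 + 2.25 + 49 = 376.7
- ratio = 0.76

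The slope as written drifts downward with time although the model is correct.

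**Step 5. Dependence on case mix.** At R² = 0.5 the residual variance is 458 × 0.5 = 229, and the prediction SD is √229 = 15.1. Suppose a held-out country had a prediction SD of 10 (assumed), the same residual variance and perfect calibration. It would score 100/(100 + 229) = 0.30 instead of 0.50. GCKD selects patients on eGFR and albuminuria while PROVALID does not select on CKD, so spread may well differ between folds.

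**The case against.** The case for leaving this alone, or grading it low, has several parts.

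- **No threshold and no recalibration.** The article fixes no pass limit, ties release of the web tool to no slope value, and plans no model updating. This stands. A model fails only in the sense of missing the conventional target, and the recalibration harm is conditional.
- **Item II exists.** It groups people by predicted risk, which is the right conditioning, and would show over-extreme risks. This is true, but it concerns the risk of fast progression and does not check the predicted eGFR values.
- **The reversed slope is not blind to miscalibration.** In general it equals r·SD(P)/SD(Y); it reduces to R² only when calibration is perfect. The correct slope is r² divided by it, so a reader could recover it if r² were also reported at each time point. This is right, but the article does not say that explained variation will be given by time point, and readers should not have to undo the definition.
- **The R² values are sample-size scenarios.** The article expects much more than 0.3. The distortion does shrink as R² rises: at an assumed R² of 0.9 the slope as written would be 0.90. It vanishes only at R² = 1.
- **The stretched model is constructed.** Shrunken predictions from about 5800 subjects are unlikely to be over-dispersed by 1.4 to 3.3 times. Agreed; it shows what the statistic rewards and is not a forecast.
- **It may be a wording slip.** Possibly, but nothing in the article corrects it, and an analyst following the text would run the wrong regression.

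**Conclusion.** The concern holds. As defined, the slope does not measure calibration of predicted eGFR. For a perfectly calibrated model it equals R², which is 0.30, 0.50 or 0.70 at the article's own scenarios, and it reaches 1.00 when predictions are over-dispersed by 1/R². These results are algebraic and rest only on taking the sample-size R² values as the R² of the predictions at a given follow-up time. The year-by-year figures and the case-mix example rest on assumed variances and serve as illustration.

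The error affects one reported statistic, in six internal-external folds and in DIACORE. It alters no coefficient, prediction or prediction interval. It should still be corrected before the analysis, because this statistic is meant to show whether the eGFR values given to clinicians and patients can be taken at face value.

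**What to change.** Reverse item I: regress actual eGFR on predicted eGFR, separately at each follow-up time, in each held-out country and in DIACORE. State the targets, slope 1 and intercept 0. It would be sensible to report calibration-in-the-large (mean observed minus mean predicted, target 0) and confidence intervals alongside; these are additions, and their absence from the article is not the fault raised here.

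Leave out baseline, or label it as a special case. The baseline value is used to form the prediction, so the slope-1 benchmark does not apply there: in the simulations above, actual on predicted at time 0 was 1.14 and 1.22 for a correct model.

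The cost is one line of text and two variables exchanged in the code. No new data are needed.
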